### Data collection methods

Data are collected at baseline (t_0_), after 3 months (t_1_ = end of intervention), and after 6 months (t_2=_primary time of assessment). A research assistant will, together with the first author, give information and training on completion of the questionnaires and data extraction from EPR at baseline. RNs/ASEs will then be responsible for filling in the questionnaires about the patients’ health condition (proxy) and extracting the data from the EPR. Organized alphabetically by last name on a list, the EPRs of the first six patients per cluster will be extracted. Time scheduled for the information meetings is 2 to 3 hours per NH. The ward manager will fill in a form on organizational characteristics. When completed, the first author and research assistant will collect the data forms. At both t_1_ and t_2_ the research assistant will deliver, give necessary additional information and collect the completed forms. NHs will be offered economic compensation for the data collection.

### Blinding

Baseline measurements will be done before randomization. A research assistant who will be blinded to group allocation will inform, deliver and collect the questionnaires/data after 3 months (t_1_) and 6 months (t_2_)_._

### Statistical analyses

Descriptive statistics will be used to present the population and the characteristics of the three groups (units, RNs/ASEs, and patients). As this is a C-RCT, the model of analysis needs to consider the effect of clustering. Analyses must also allow for inclusion of covariates at both the individual and cluster level. Relevant covariates at the individual level in a multiple logistic regression model are age, sex, length of stay in NH, cognitive performance, mobility, functionality, diarrhea, constipation. Hence, this study will use mixed effect models with the cluster treated as a random effect. Analyses will be computed using Stata 12.1.

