### Aims and objectives

The overall aim of this study is to achieve a reduction in bowel leakage and accidents for NH patients by altering the quality of continence care among registered nurses (RNs), authorized social educators (ASEs, see below), and care staff in general. The primary objective is to test the hypothesis that a multifaceted educational program for NH care staff on assessment and treatment of FI reduces patients’ frequency of FI.

Secondarily, the trial will investigate the effect of a multifaceted educational program for NH care staff on 1) remission of FI among patients with FI present at baseline or the incidence of new cases of FI among patients identified as continent at baseline; 2) change in NH patients’ FI-related concerns such as mood, constipation, diarrhea and skin condition; 3) increased knowledge among RNs and ASEs; 4) change of practice among RNs, ASEs and care staff in general; 5) and reduction in costs related to FI management. The study also intends to investigate correlates of FI in the NH population.

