#### Content of the multifaceted intervention

*The FI-guideline* is based on best practice recommendations [1,13,32,33] and will be introduced to the RNs/ASEs in the intervention NHs during the workshop (see below). The FI-guideline facilitates a systematic assessment of bowel symptom history and bowel patterns. As FI among NH patients is considered to have a complex etiology, the guideline encourages the RN/ASE to consider a range of possible causes. Examples are loose stools, immobility, cognitive impairment, impaction and use of laxatives. Based on this assessment, the RN/ASE defines a nursing diagnosis, for example: ‘FI related to loose stools, possibly due to excessive laxatives, urgency and reduced mobility. This leads to FI episodes with loose stool and red perineal skin’. The guideline then offers a range of possible interventions. The result of the paper-based assessment, the nursing diagnosis and interventions, is then documented in the patient’s EPR as an individualized care plan.

*One one-day educational meeting* (7 hours) is defined by the Cochrane Effective Practice and Organization of Care (EPOC) as ‘participation of healthcare providers in conference, lectures, workshops or traineeships’ [14]. The educational meeting will be organized as an interactive workshop, which targets knowledge, attitudes, and skills. The workshop will be conducted in a local meeting room in each intervention NH. Part one of the workshop includes the RNs/ASEs filling in a knowledge test (which is part of the data collection). However, by organizing it as a part of the workshop, the pedagogical intention is to facilitate learning, as it is possible to find the answers in the following theoretical input. Part two of the workshop is case-based discussion concerning the FI-guideline. As individualization of the nurse’s diagnoses and the interventions is essential, an important pedagogical intention is to empower the RNs/ASEs’ clinical and critical thinking. Another important issue is how to integrate the use of the guideline with the electronic patient record (EPR) system. The topics for the educational meeting, including the FI-guideline, will be made available for the staff as printed educational material [14].

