The study has the following secondary outcome measures:*Remission of FI* among patients identified with FI at baseline, or *incidence* of new cases of FI among patients identified as continent at baseline, measured by interRAI LTCF section H3 and the St Marks score.*Change in FI related concerns* measured by interRAI LTCF: section E: Mood and behavior, section F: Psycho-social wellbeing, section H1: Urinary continence, section J: State of health - Constipation and diarrhea, section L: Skin condition, and section M: Participation in activities.*Change in knowledge* among RNs/ASEs measured by multiple choice tests developed by the researchers according to established guidelines [38].*Change in documented care for FI by health personnel as registered in the EPR*: RNs/ASEs will extract data from the EPR. The instrument N-Catch [39] will be used for this purpose. N-Catch is an audit instrument for nursing reports in the EPR. N-Catch is translated into Norwegian and developed based on the validated D-Catch [40] and Cat-ch-ing [41]. Change in care will also be measured by the Fecal Incontinence in Nursing Home Patients questionnaire [6] where RNs/ASEs are offered a list of interventions for FI, urinary incontinence, diarrhea and constipation and asked to identify what is done for each individual patient.*Change in cost* of FI management measured by mapping the use of products (diapers, pads, plugs) and bowel medications measured by interRAI LTCF section H: Continence - remedies, section N: Medications, and the Fecal Incontinence in Nursing Home Patients questionnaire.*Correlates of FI* among NH patients measured by interRAI LTCF: section C: Cognitive functioning, section D: Communication and vision, section G: Functionality and mobility, section I: Medical diagnoses, section J: Health condition, section K: Mouth- and nutrition status, section N: Medications, and section O: Treatment, examinations/procedures.

Process evaluation will include attendance at the pedagogical program and use of the FI-guideline. Evaluation will be conducted by using checklists administered by the researchers: proportion RNs/ASEs within eligibility criteria participating in the workshop, proportion of staff participating in the educational outreach meetings, proportion of patients assessed by the FI-guideline, and proportion of patient assessments resulting in an individualized care plan in the EPR.

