#### Primary outcome

As a consequence of the dichotomization of the variable, the primary outcome will be analyzed according to a mixed logistic binominal model. The model will be fitted by maximum likelihood. Because of the relatively high risk of deaths and movement out of clusters, data will be treated as a cross-sectional time series, with the prevalence among all patients present in the cluster at baseline included as a covariate in the analyses.

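### Diarrhea, constipation, mobility and functionality are listed as model covariates without limiting them to pre-randomization values, although the first two are outcomes the programme is meant to change

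*Protocol article*

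**What the plan says.** Under Statistical analyses the protocol article states that "Analyses must also allow for inclusion of covariates at both the individual and cluster level". It then names the relevant individual-level ones for a multiple logistic regression model, "age, sex, length of stay in NH, cognitive performance, mobility, functionality, diarrhea, constipation", and gives this as the reason for using mixed effect models. No measurement time is attached to the list.

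The Primary outcome subsection specifies a mixed logistic model in which "data will be treated as a cross-sectional time series". Only one covariate is named there, and it is explicitly a baseline quantity: the model is to be fitted "with the prevalence among all patients present in the cluster at baseline included as a covariate in the analyses".

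Two of the listed covariates appear elsewhere as effects to be measured. Aims and objectives includes change in "FI-related concerns such as mood, constipation, diarrhea and skin condition", and Outcome measures assigns these to interRAI LTCF "section J: State of health - Constipation and diarrhea". The description of the FI-guideline gives the causes that staff are asked to consider: "Examples are loose stools, immobility, cognitive impairment, impaction and use of laxatives".

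Functionality and mobility (interRAI section G) appear in Outcome measures only under correlates of FI.

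**The concern.** Bowel symptoms are given two roles: something the programme should change, and something to hold constant in the model type used to estimate its effect. If the values held constant are those recorded after allocation, the adjusted treatment odds ratio no longer estimates the programme's whole effect on FI. It estimates what remains once any effect passing through those symptoms is taken out, and treating loose stools or impaction is one of the routes by which the guideline would be expected to work.

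The text leaves an analyst free to include or omit these terms, and to use baseline or 6-month values. Those choices can give materially different estimates for the primary outcome.

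**Working it through.** **Step 1. Set the passages side by side.**

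- Diarrhea and constipation: covariates in Statistical analyses, secondary outcomes in Aims and objectives and in Outcome measures. Loose stools, impaction and laxative use are also guideline causes. The conflict is direct.
- Mobility: a covariate. Immobility is a guideline cause, but mobility is not an effect outcome. The support is weaker.
- Functionality: a covariate, listed otherwise only as a correlate. Nothing says the programme acts through it.

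**Step 2. Ask which values are available.** The Blinding section puts baseline measurement before randomization, so baseline values would be safe. But Methods/design describes a repeated cross-sectional design, and the primary data are cross-sectional because of deaths and movement out of clusters. A patient admitted after baseline has no individual baseline value. Adjusting everyone present at 6 months at the individual level must then either use post-allocation values or drop the new admissions.

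**Step 3. Illustrate the size.** The plan gives no figure for this, so there is none to reproduce.

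Inputs:

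- From Sample size: a difference of 15%, read as percentage points.
- Assumed: FI in 50% of control and 35% of intervention patients (the article gives no control proportion); one binary symptom with prevalence q0 in control and q1 in intervention; symptom-FI odds ratio R.

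Marginal odds ratio = (0.35/0.65)/(0.50/0.50) = 0.54; log = -0.619.

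With e(x) = 1/(1+exp(-x)) and g = ln R, solve for a and b:

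- 0.50 = (1-q0)·e(a) + q0·e(a+g)
- 0.35 = (1-q1)·e(a+b) + q1·e(a+b+g)

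The adjusted odds ratio is exp(b), and the share of the log odds ratio removed is 1 - b/(-0.619).

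First row in full (40% to 20%, R = 3):

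- a = -0.434, so control FI is 39.3% without and 66.0% with the symptom: 0.6×0.393 + 0.4×0.660 = 0.50.
- b = -0.425, so intervention FI is 29.8% and 56.0%: 0.8×0.298 + 0.2×0.560 = 0.35.
- exp(-0.425) = 0.65; share removed = 1 - 0.425/0.619 = 31%.

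| Symptom prevalence, control to intervention | R | Adjusted OR | Log OR removed |
|---|---|---|---|
| 40% to 20% | 3 | 0.65 | 31% |
| 40% to 20% | 4 | 0.68 | 39% |
| 30% to 15% | 4 | 0.64 | 28% |
| 40% to 30% | 3 | 0.58 | 12% |

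**Step 4. Check on another scale and starting point.** With FI at 45% versus 30%, the difference at equal symptom prevalence (the average of the two arms) is 13.7 points if symptoms fall from 30% to 25% with R = 3, since 1 - 13.7/15 = 9% is removed. It is 7.5 points if they fall from 40% to 20% with R = 5, where 50% is removed. If the symptom has the same prevalence in both arms, as expected for a pre-randomization value, the full 15 points remain.

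**Step 5. Check the direction.** If recorded symptoms rise from 30% to 40% (R = 3, FI 50% versus 35%), the adjusted odds ratio is 0.46, further from 1 than 0.54. A small part of that shift arises only because a covariate-adjusted odds ratio differs from a marginal one: with prevalence unchanged at 30% the adjusted value is 0.52. The rest comes from conditioning on the changed symptom.

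**The case against.** The strongest reply is that the article does not commit to a biased analysis. The covariate paragraph is general, it justifies a class of model, and it gives no measurement time. The Primary outcome subsection names only baseline cluster prevalence. Most of the non-demographic covariates also match interRAI sections listed for the correlates analysis, where follow-up values would be unobjectionable. Covariate timing is a detail that an article often leaves to the full plan.

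Much of this stands. A reader might infer that part of the effect will be adjusted away in the primary analysis. The documents do not support that: it needs follow-up values and a programme effect on the symptoms, and neither is stated. A reader might also treat mobility and functionality as established mediators. Immobility is only a cause to be considered, and functionality is not named as a target at all. Nor is a bias toward no effect certain. The Discussion warns that educated staff may recognize FI more often, and the same group of RNs/ASEs fills in the patient questionnaires, so recorded symptoms could rise.

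What does not fall away is that the article goes beyond silence. It names two of its own outcomes as covariates for a logistic model, in a section that governs all analyses, and pairs this with a design in which baseline values do not exist for every patient analysed.

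**Conclusion.** The point holds as a conditional one. The list admits post-allocation diarrhea and constipation into between-arm models, and the cross-sectional design makes that the likely result if the list is applied to all patients present at 6 months. The estimate would then be biased, most likely toward no effect if the programme lowers the symptoms, possibly away from it if trained staff record more of them.

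The size cannot be established from the documents. The range of 12% to 39% of the log odds ratio rests on assumed FI proportions of 50% and 35%, assumed falls in symptom prevalence of 10 to 20 points, and an assumed symptom-FI odds ratio of 3 to 4. The case is firm for diarrhea and constipation, moderate for mobility, and precautionary for functionality.

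**What to change.** Add one sentence to Statistical analyses. The between-arm models adjust only for:

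- baseline cluster FI prevalence, as the Primary outcome subsection already says;
- characteristics that allocation cannot change, such as age and sex;
- if wanted, pre-randomization values of other variables, summarized at cluster level in the cross-sectional models or used individually in the cohort analyses of remission and incidence, where every patient has a baseline record.

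State that follow-up diarrhea, constipation, mobility and functionality enter no between-arm effect model and are kept for the correlates-of-FI analysis. Place length of stay and cognitive performance explicitly under the same rule.

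The change needs no new data. Its cost is slightly less individual covariate adjustment for patients admitted after baseline. It should be settled before the outcome data are analysed.

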#### Primary outcome

As a consequence of the dichotomization of the variable, the primary outcome will be analyzed according to a mixed logistic binominal model. The model will be fitted by maximum likelihood. Because of the relatively high risk of deaths and movement out of clusters, data will be treated as a cross-sectional time series, with the prevalence among all patients present in the cluster at baseline included as a covariate in the analyses.

#### Secondary outcomes

For remission of FI a cohort approach to data analyses with repeated measures with only those identified with FI at baseline and still present at 3 and 6 month follow-up will be included and analyzed according to a mixed logistic binominal model. For incidence of FI a cohort approach to data analyses with repeated measures with only those identified as continent at baseline and still present at 3 and 6 month follow-up will be included and analyzed according to mixed logistic binominal model. For change in FI-related concerns, change in knowledge among RNs/ASEs, change in care, and change in cost the outcomes, dependent on whether they are continuous, ordered or binary, will be treated as cross-sectional time-series and analyzed according to mixed effects models. Correlates of FI will, dependent on whether they are continuous, ordered or binary, be analyzed according to mixed effect models.

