### Sample size

Sample size calculations are based on the primary outcome: frequency of FI among patients. The power calculations have taken into account the results from the pilot study. The pilot study identified the primary outcome variable to be skewed to the right, and methodological consideration resulted in a dichotomization of the primary outcome variable with a cut off between 2 (continent, continent with a stoma and seldom incontinent) and 3 (occasionally incontinent, often incontinent and incontinent). Based on results from the pilot study, we hypothesized that a reasonable and clinically important effect size in the intervention group compared to the control group would be 15% between the two groups in proportions with FI (score of 3 to 5). As the design is a cluster randomized trial, we need to adjust for clustering. The intracluster correlation coefficient (ICC) is estimated to be 0.04. The estimate is based on published patterns in ICCs [23,42-44], and results from the pilot study where the ICC was calculated to be 0.038. In addition, we had access to the FI variable with the categories 0 to 4 from an epidemiological study of 980 NH patients in Trondheim municipality [6] with an ICC calculated as 0.028. Based on the assumptions of the mixed logistic binominal model, 5% level of significance, test strength of 80%, an average cluster size of 15 patients, and an ICC of 0.04, a study population of 103 patients in each arm of the C-RCT is needed. The number of individuals in each cluster is set because each unit has a fixed number of beds. Assuming a 15% dropout, the sample needed is 120 patients in each arm. This means a total of 240 patients and about 20 NH units (Figure 1).

In addition, the number of patients records needed for data extractions, was calculated. N-Catch measures the quality of the content in the EPR on a scale from 0 to 32 where 0 is low quality and 32 is high quality [39-41]. Based on the assumption of a paired *t*-test, a 5% level of significance, test strength of 80%, an effect size of 3 points and an ICC of 0,04, records from 6 patients per cluster is needed for a total of 146 records (Figure 1).

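### Remission and incidence are restricted to patients present at both 3 and 6 months, which drops usable 3-month outcomes of patients who leave later

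*Protocol article*

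**What the plan says.** The Secondary outcomes section of the protocol article describes the remission analysis as follows: "For remission of FI a cohort approach to data analyses with repeated measures". It then fixes who enters: "only those identified with FI at baseline and still present at 3 and 6 month follow-up will be included". For incidence the condition is the same: "only those identified as continent at baseline and still present at 3 and 6 month follow-up will be included". Both outcomes are to be analysed with a mixed logistic model.

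The Primary outcome section shows that attrition was foreseen. It reads "Because of the relatively high risk of deaths and movement out of clusters, data will be treated as a cross-sectional time series", so the primary analysis does not follow a closed cohort. The only attrition figure is in Sample size: "Assuming a 15% dropout, the sample needed is 120 patients in each arm".

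Under Randomization and allocation and under Blinding, baseline measurement precedes randomisation. Baseline FI status is therefore a legitimate basis for a subgroup. Presence at 3 and 6 months is not known until after allocation.

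**The concern.** The rule adds two conditions to a cohort defined before randomisation: presence at 3 months and presence at 6 months. The second costs data. Someone assessed at 3 months who leaves before 6 months has an observed remission or incidence outcome. A repeated-measures mixed model accepts patients with one follow-up visit, so nothing in the planned method calls for removing that person, and the article gives no reason for it.

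The rule also means that the 3-month comparison is made in a set selected by what happens between 3 and 6 months. If departures in that interval are related both to arm and to the course of FI, the 3-month comparison inherits a selection that could have been avoided. Precision and a weaker missing-data assumption are at stake for two secondary outcomes. The primary outcome is not affected.

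**Working it through.** **Attrition figure in the plan.** Sample size states that "a study population of 103 patients in each arm of the C-RCT is needed", raised to 120 per arm for 15% dropout.
- 103 / (1 - 0.15) = 121.2, rounded up to 122.
- 103 x 1.15 = 118.5, rounded up to 119.
- The stated 120 lies within 2 patients of both, so 15% is the working dropout rate. The plan states it for the primary sample size. Applying it to the cohorts is an assumption.

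**Inputs for the cohorts**
- Total 240 patients (Sample size: "This means a total of 240 patients and about 20 NH units").
- FI at baseline 40-55%. This is the literature range in the Background, assumed here because the article gives no baseline figure for this trial.
- The continent cohort is taken as everyone else, also an assumption.
- Loss L by 6 months: 15%, with 30% as an assumed upper value.
- Constant rate of loss, so the proportion present at 3 months is the square root of (1 - L). For L = 15% this is 0.922; for L = 30% it is 0.837.

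**Cohort sizes.** FI: 240 x 0.40 = 96 to 240 x 0.55 = 132. Continent: 144 down to 108.

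**Patients with a 3-month outcome who are dropped** = n x [square root of (1 - L) - (1 - L)].

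| Loss by 6 months | Cohort | n | Present at 3 months | Present at both | Dropped with a 3-month outcome |
|---|---|---|---|---|---|
| 15% | FI | 96 / 132 | 88.5 / 121.7 | 81.6 / 112.2 | 6.9 / 9.5 |
| 15% | Continent | 144 / 108 | 132.8 / 99.6 | 122.4 / 91.8 | 10.4 / 7.8 |
| 30% | FI | 96 / 132 | 80.3 / 110.4 | 67.2 / 92.4 | 13.1 / 18.0 |
| 30% | Continent | 144 / 108 | 120.5 / 90.4 | 100.8 / 75.6 | 19.7 / 14.8 |

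**Share of observations lost**
- 3-month observations: 1 - 0.85/0.922 = 7.8% at 15% loss; 1 - 0.70/0.837 = 16.3% at 30%.
- All follow-up observations: 1 - 2 x 0.85/(0.922 + 0.85) = 4.1% at 15% loss; 8.9% at 30%.

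**What cannot be recovered.** In the FI cohort at 15% loss, the rule excludes 96 x 0.15 = 14.4 to 132 x 0.15 = 19.8 patients. Subtracting the recoverable 6.9 to 9.5 leaves 7.5 to 10.3 who go before 3 months and have no follow-up under any rule. About half of the exclusions can be reversed.

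**When arms would be biased (invented rates, no treatment effect).** Suppose 70% of the FI cohort remit with probability 0.25, 30% are frail and remit with probability 0.05, and only frail patients leave. Remission in the whole cohort is 0.7 x 0.25 + 0.3 x 0.05 = 19%. Among completers it is [0.175 + (0.3 - L) x 0.05]/(1 - L).
- Loss of 15% in both arms: 0.1825/0.85 = 21.5% in each, a difference of zero.
- Loss of 10% and 20%: 0.185/0.90 = 20.6% and 0.180/0.80 = 22.5%, a false difference of about 2 points.

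With equal loss the level shifts but the contrast does not. A false contrast needs loss that differs by arm and is related to FI course. Nothing in the article shows that it will.

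**The case against.** **The wording may be looser than it looks.** The phrase could mean present at each visit in turn, in which case no 3-month result is lost. That reading is possible. But the sentences define a set of patients to include, and the natural reading is presence at both visits. If the looser sense was meant, the only change needed is to say so.

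**Restricting to patients still present is a defensible choice when deaths are common.** A likelihood-based model that assumes data missing at random implicitly carries outcomes forward for patients who have died. This stands, and it limits how the result may be read. It does not justify deleting an outcome observed while the patient was alive and in the unit.

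**The recoverable loss is modest.** This also stands: about 4% of follow-up observations at the planned dropout.

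**Stronger readings that the article does not support**
- A reader might infer that the rule demonstrably biases the treatment comparison, or overstates remission and understates incidence. That needs leavers to have a worse FI course, which is plausible but stated nowhere. Bias between arms further needs loss related to arm.
- A reader might infer that a completers analysis is valid only if data are missing completely at random. That is not generally so. A regression on completers can be valid when loss depends on arm and modelled covariates but not, given these, on the outcome. Statistical analyses lists age, length of stay, cognitive performance, mobility and functionality, which may account for part of the loss.
- A reader might infer that admitting everyone with one follow-up restores the full randomised cohort. It does not, because patients lost before 3 months still contribute nothing.
- The Primary outcome section should not be read as a second instance of the problem. Its cross-sectional approach is a response to deaths and movement.

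**Conclusion.** The point holds in limited form. Taken literally, the inclusion rule discards 3-month outcomes that the planned model can use, and it selects the 3-month comparison by presence at 6 months. The size is about 7-10 patients per cohort, 8% of 3-month observations and 4% of all follow-up observations. This rests on 240 patients, 40-55% FI at baseline, 15% loss by 6 months, a constant rate of loss and complementary cohorts. At an assumed 30% loss it would be about 13-20 patients per cohort, 16% and 9%.

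Bias between arms is possible but not shown. The consequence that can be stated with confidence is avoidable loss of precision and a stronger missing-data assumption than needed, on two secondary outcomes.

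**What to change.** In Secondary outcomes, replace the condition of presence at both visits with the following:
- Include every patient in the baseline-FI cohort (for remission) or the baseline-continent cohort (for incidence) with at least one follow-up assessment.
- Fit the repeated-measures mixed logistic model with the individual-level covariates listed under Statistical analyses, at their baseline values, and a patient-level random effect in addition to the cluster effect. The patient effect links a patient's two visits, so that the 3-month result informs the analysis of those who leave later.
- Report deaths and departures by arm and interval.
- Keep the analysis of patients present at both visits as a sensitivity analysis.
- State that the results apply to patients while present in the unit, since conditioning on presence at 3 months remains.

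The cost is a change of wording and a little more analysis. No extra data are needed, because 3-month assessments are already scheduled under Data collection methods. The revised model relies on missing at random for patients who leave after 3 months, and the sensitivity analysis helps to show how much that matters.
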